#### Recruitment

The UH student well-being services are available to all students at the university, and there are no exclusion criteria for the study. All the students willing to participate are included regardless of their level of loneliness, state of psychological well-being, or stage of studies. Students are recruited for the active intervention groups and no-intervention group by email, website, and social media advertisements circulated by the UH media and communications services, communications services at the faculties, student health services, and student organizations. The students are not randomly assigned to the intervention groups and can sign up for a course of their choice. The facilitators of the G4H intervention are also invited to participate in the study during the G4H facilitator training. All facilitators willing to participate are included in the study. Taking part in relevant concomitant care is not prohibited during the intervention study. The participating students or facilitators are not blinded to the study protocol.

### Quantitative Methods

To collect the quantitative data, we use paper-and-pencil and electronic versions of the questionnaires. Those in the active intervention groups fill out the questionnaires before or after the intervention sessions if the questionnaires are provided electronically and during the session if the questionnaires are provided on paper. Those in the no-intervention group fill out the questionnaires based on the email reminders of the electronic data collection system (time interval between reminders is the same as the interval between sessions in the active intervention groups).

Electronic data collection is implemented in the Research Electronic Data Capture (REDCap) system (Vanderbilt University) [41], provided by the UH for collecting sensitive research data electronically. In the case of the TBWS intervention, data collection from time points before and immediately after the intervention is partly integrated into the online course platform, and the students can respond either via the course platform or via the REDCap system, while data collection from week 3 and the 1- and 3-month follow-ups is implemented only in the REDCap.

Before the analysis phase, the data validity is confirmed via range checks, missing value checks, and outlier detection. Potentially erroneous data are checked against the paper and electronic forms, and other necessary sources, and corrected if needed. All modifications are documented.

Participant retention is promoted by reminding the participants during the group meetings to fill out the questionnaires. All participants receive up to 5 reminder messages from the electronic data collection system if they do not complete the necessary questionnaires on time. Retention is also promoted by the possibility of receiving written feedback on the questionnaire results after participation. Participating students also receive movie tickets as compensation for completing all follow-up questionnaires. Adherence to the G4H intervention is monitored by documenting the number of sessions in which each student participated.

All the quantitative methods used are presented in Table 1, which also includes the measurement time points and study arms from which the data are collected. Multimedia Appendix 1 includes a table that describes the unabbreviated titles of each scale, scale details, and information on their reliability and validity. Most measures have demonstrated at least acceptable internal consistency (Cronbach α≥0.70) and convergent validity with other similar measures. The few exceptions with lower Cronbach α are either very short scales (4 items) or include a specific subscale that performs poorly.

**Table 1. T1:** The quantitative assessment design including areas of assessment, used measures, and an assessment schedule

Assessment	Scales, forms, and measures	Time points and arms (1-4)^a^ where data are collected						
		Week 1	Week 2	Week 3	Week 4	Week 7	1-month follow-up	3-month follow-up
Primary outcome measures								
Loneliness	ULS-8^b^ [42]	1‐4	—	—	—	1‐4	1‐4	1‐4
Loneliness	ULS-4^c^ [43]	1‐4	—	1‐4	—	1‐4	1‐4	1‐4
Depression	PHQ-9^d^ [44]	1‐4	—	—	—	1‐4	1‐4	1‐4
Secondary outcome measures								
Active group memberships	EXITS^e^ [45]	1‐4	—	1‐4	—	1‐4	1‐4	1‐4
Mental well-being	SWEMWBS^f^ [46]	1‐4	—	—	—	1‐4	1‐4	1‐4
General well-being	GP-CORE^g^ [47]	1‐4	—	—	—	1‐4	1‐4	1‐4
Anxiety	GAD-7^h^ [48]	1‐4	—	—	—	1‐4	1‐4	1‐4
Social anxiety	Mini-SPIN^i^ [49]	1‐4	—	—	—	1‐4	1‐4	1‐4
Quality of life	EQ-5D-5L^j^ [50]	1‐4	—	—	—	1‐4	—	1‐4
Use of social and health care services	Health service usage self-report (medications, health care appointments, hospitalization, and counseling)	1‐4	—	—	—	1‐4	—	1‐4
Time used by facilitators	Time used at planning, executing, and assessing the sessions	1	1	1	1	1	—	—
Study credits	UH^k^ registries, 1 year before and 1 year after the intervention (arms 1‐4)	—	—	—	—	—	—	—
Grade point average	UH registries, 1 year before and 1 year after the intervention (arms 1‐4)	—	—	—	—	—	—	—
Weighted grade point average	UH registries, 1 year before and 1 year after the intervention (arms 1‐4)	—	—	—	—	—	—	—
Other outcome measures								
Identification with the intervention group	SISI^l^ [51]	—	—	1‐3	—	—	—	—
Participants’ working alliance	WAI-SR^m^ [52]	—	—	1‐2	—	—	—	—
Facilitators’ working alliance	WAI-SRT^n^ [53]	—	—	1	—	—	—	—
Mood	Analog mood scale (0‐7)	1‐4		1‐4		1‐4	1‐4	1‐4
Fidelity to the G4H manual	G4H^o^ manual fidelity checklist	1	1	1	1	1	—	—
Participant attendance	Number of sessions participated	1	1	1	1	1	—	—
Background variables								
Participant background								
Sociodemographic characteristics	Gender, birth date, mother tongue, marital status, household composition, residential situation, employment status, education, income, subjective financial situation, subjective health, subjective loneliness, and subjective minority status	1-4	—	—	—	—	—	—
Social support	SSQ3^p^ [54]	1‐4	—	—	—	—	—	—
Treatment motivation	SIMS^q^ [55], tailored motivation rulers [56]	1‐3	—	—	—	—	—	—
Organized studying	4 items from a HowULearn questionnaire [57]	1‐4	—	—	—	—	—	—
Facilitators’ assessment								
Sociodemographic characteristics	Gender, birth date, mother tongue, marital status, household composition, residential situation, employment status, education, and income	—	—	—	—	—	—	—
Professional and individual characteristics	XS5^r^ [58], ECR-S^s^ [59], TBIF-PI^t^ [60]	1	—	—	—	—	—	—
Self-assessed skillfulness	TWIS^u^ [61]	—	—	1	—	—	—	—

a Arm 1: Groups 4 Health intervention; arm 2: study psychologists’ group interventions; arm 3: toward better well-being and studying intervention; and arm 4: mo-intervention control group.

b ULS-8: 8-item University of California Los Angeles Loneliness Scale.

c ULS-4: 4-item University of California Los Angeles Loneliness Scale.

d PHQ-9: Patient Health Questionnaire.

e EXITS: Exeter Identity Transition Scales

f SWEMWBS: Short Warwick-Edinburgh Mental Well-being Scale.

g GP-CORE: General Population version of the Clinical Outcomes in Routine Evaluation –scale

h GAD-7: Generalized Anxiety Disorder -questionnaire.

i Mini-SPIN: Mini Social Phobia Inventory.

j EQ-5D-5L: EuroQol - 5 dimension - 5 level questionnaire.

k UH: University of Helsinki.

l SISI: Single-Item Social Identification measure.

m WAI-SR: Working Alliance Inventory Short and Revised.

n WAI-SRT: Working Alliance Inventory Short and Revised Therapist version.

o G4H: Groups 4 Health.

p SSQ3: Social Support Questionnaire (three-item version).

q SIMS: Situational Motivation Scale.

r XS5: Extra-Short Five.

s ECR-S: Experiences in Close Relationships Short form.

t TBIF-PI: Personal Identity scale of the Trainee Background Information Form.

u TWIS: Therapist Work Involvement Scales.

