**Methods:**

The quantitative part of the study is a 4 parallel-arm nonrandomized controlled trial aiming to recruit 600 student participants from the University of Helsinki. The experimental group, which receives the G4H intervention, includes 5 group meetings held over a 7-week period. The experimental group will be compared with 2 active comparators: groups organized by the University of Helsinki study psychologists and a 7-week online intervention course focused on well-being and study skills, and to a no-intervention control group. The primary quantitative outcomes of the study are loneliness and depression; secondary outcomes include several measures of students’ well-being, academic performance, and cost-effectiveness of the intervention. Quantitative data are collected before the intervention, during the intervention (at week 3), immediately post intervention (at week 7 after baseline), and at 1- and 3-month follow-ups. The qualitative part of the study explores the challenges and opportunities related to inclusion and equality identified in the G4H intervention using observations, interviews, and focus group discussions.

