#### Secondary Outcomes

The secondary outcomes are active group memberships, mental well-being, general well-being, anxiety, social anxiety, academic performance, health-related quality of life, use of social and health care services, intervention costs, and cost-effectiveness of the intervention (refer to Table 1 and Multimedia Appendix 1 for details).

To assess participants’ academic performance, data will be retrieved from the UH student register (Sisu student information system). Academic performance is determined by 3 outcome variables: overall accumulated study credits, the grade point average (GPA) of the study credits and the weighted GPA. When determining the weighted GPA, only completed studies that have been assessed on a numeric scale (from 1 to 5) are considered, as some courses accumulate study credits but are graded only as passed or failed. Weighted GPA is determined by the grades of each course weighted by the number of credits gained for it. The academic performance data are collected from 2 time periods: a 1-year period before and a 1-year period after starting the assigned intervention (baseline, week 1).

Cost-effectiveness analyses will apply a societal perspective by including intervention costs as well as university students’ health and social services costs. For the cost-effectiveness analyses, the facilitators will provide information on the time used for planning, executing, and assessing the sessions to evaluate the costs of the G4H intervention. Furthermore, the students in all trial arms fill out 2 questionnaires before the intervention, immediately after the intervention, and at 3-month follow-up (Table 1). The questionnaires measure health-related quality of life and self-reported use of health and social services (Table 1). The use of health and social services will be monetarized using Finnish national unit costs [62].

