### Ethical Considerations

#### Overview

The study protocol was approved by the Research Ethics Committee in the Humanities and Social and Behavioural Sciences at the UH, Finland (Statements: 15/2022, 32/2023, 10/2025). The ethical board will be informed in case of important protocol modifications. Written informed consent to participate in the study is obtained from all participants and facilitators. The participants are informed about the study via an information sheet and a data protection notice detailing the research protocol, data management, and participants’ rights following the General Data Protection Regulation (GDPR) of the European Union. The consent form can be signed electronically or on paper. Electronic consent forms are delivered via an email from the REDCap system before the first intervention session or at a corresponding time point for the control group. Paper consent forms are delivered during the first meeting of each active intervention. The participants are also told that they may be contacted about potential ancillary studies. The participants are informed that they can withdraw from the study at any point without any consequences. The participants receive movie tickets as compensation for participating. A data monitoring committee has not been appointed as there is no suspicion of harm caused by the interventions studied in this trial to the participants.

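### The stated completion rules let the G4H and SPG baseline fall in or after session 1, although it is described as collected before the intervention

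*Protocol article*

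**What the plan says.** The protocol article describes the timing of baseline in several places.

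- **Abstract, Methods:** "Quantitative data are collected before the intervention".
- **Secondary Outcomes**, on quality of life and service use: "the students in all trial arms fill out 2 questionnaires before the intervention". The same section, when defining the registry periods, equates baseline with week 1 and with the start of the intervention.
- **Quantitative Methods**, active arms: forms are completed "before or after the intervention sessions if the questionnaires are provided electronically and during the session if the questionnaires are provided on paper". The sentence covers all assessments and does not treat week 1 separately. Late responders get up to 5 reminders, and no cut-off at session 1 is given.
- **Quantitative Methods**, controls: "Those in the no-intervention group fill out the questionnaires based on the email reminders of the electronic data collection system".
- **Ethical Considerations, Overview:** "Electronic consent forms are delivered via an email from the REDCap system before the first intervention session", whereas "Paper consent forms are delivered during the first meeting of each active intervention". Written consent is required from every participant.
- **Participants' safety:** TBWS students have their well-being assessed at the start of the course. Under Quantitative Methods, that arm's pre-intervention form is answered on the course platform or in REDCap.
- **Strengths and Limitations:** the article concedes that differing collection methods may cause mode effects and measurement bias, and promises sensitivity analyses. It does not mention baseline timing.

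**The concern.** The description of baseline and the operating rule for completing it do not agree. One says that baseline comes before the intervention. The other allows it to be filled in while a session is running or after it has ended.

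This matters more here than in a randomized trial.

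- Students choose their arm, so the analysis relies on background and baseline data to adjust for selection. Statistical Analyses also uses baseline symptoms to model dropout. A variable already touched by exposure is weaker in both roles.
- The first G4H module is psychoeducation on why group memberships matter for health. That is close to loneliness (primary) and active group memberships (secondary), both measured at week 1 according to Table 1.
- Treatment motivation is measured at week 1 in arms 1 to 3 and is hypothesised to predict engagement and effect. Measured after a session, it would be partly a response to that session.
- Controls have no session, so any shift would fall on one side of each comparison with control.

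**Working it through.** The article gives no figure on this point to reproduce. The check is a comparison of the stated rules, followed by an illustration on assumed values.

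**Step 1. When can baseline occur on each route?**

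| Arm and route | What the rules allow at week 1 |
|---|---|
| G4H or SPG, electronic consent and form | Consent form is sent before session 1. The questionnaire may be completed before or after sessions, with no cut-off. Before session 1 is possible; after it is not excluded. |
| G4H or SPG, paper consent and form | Consent at the first meeting, form filled in during the session. At the earliest in session 1; order relative to the content is not stated. |
| G4H or SPG, paper consent, electronic form | Cannot precede the first meeting; completion after it is permitted. |
| TBWS | Online, at the start of the course. Late only if completed after course content begins. |
| Control | Email prompt; no session. |

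**Step 2. To whom does the session wording apply?** Arm sizes at the first data freeze (Study Status) are G4H 155, SPG 125 and TBWS 216. The session-based arms hold 155 + 125 = 280 of 155 + 125 + 216 = 496 active participants, which is 280/496 = 56%. TBWS holds 216/496 = 44%. The 56% is the group to which the wording can apply, not an estimate of late baselines.

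**Step 3. What would a late baseline do?** Let E be the true effect on change against control, p the share of an arm's baselines taken after session 1, and s the share of E already present after session 1. The follow-up mean is unaffected. The baseline mean has moved by p × s × E, so

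observed change against control = E − p × s × E = E × (1 − p × s).

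Neither p nor s is in the document. Assume p from 0 to 1. Assume s from 0 to 0.20, the upper value being one of five G4H sessions taken as equally effective (Arm 1 describes five sessions).

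- p = 0 or s = 0: understated by 0%.
- p = 0.5, s = 0.10: 0.5 × 0.10 = 5%.
- p = 0.5, s = 0.20: 0.5 × 0.20 = 10%.
- p = 1, s = 0.20: 1 × 0.20 = 20%.

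**Step 4. Direction.** With a beneficial first session (s > 0), change against control is understated. If the first session briefly worsened answers (s < 0), it would be overstated. Between G4H and SPG the shifts partly cancel if both arms follow the same procedure.

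**The case against.** The strongest reply is that the completion rule is one sentence covering weeks 1, 3 and 7 together, so it can be read as before the session at week 1 and after it later. The abstract and Secondary Outcomes then fix baseline explicitly. Electronic consent forms go out before session 1. Paper consent at the first meeting shows only that these baselines do not precede arrival; forms handed out at the start would still precede the content. Figure 1, which places assessments against meetings, is not visible in the text reviewed and may settle the order. TBWS, the largest active arm, has no facilitated meeting in which paper forms would be filled in. Mode effects are already acknowledged.

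Much of this stands. The text does not show that any baseline followed session content, TBWS largely falls outside the session wording, and the general mode issue is already conceded. It does not remove the point. The favourable reading has to be supplied by the reader, because no sentence puts week 1 forms ahead of session 1 content or closes the electronic form when the session starts. The acknowledged limitation concerns how data are collected, not whether baseline precedes exposure.

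**Conclusion.** The point holds as a conflict between stated rules. For G4H and SPG, the completion and consent procedures permit a baseline in or after session 1, while the article describes it as before the intervention. It should be reconciled, but it is not a demonstrated bias.

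The size is unknown and could be zero. The 0% to 20% understatement rests on assumed values for the share of late baselines and for the effect of the first session. It is not a bound that the document supplies.

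A reader might infer more, and the document does not support it:

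- **That baselines were in fact contaminated.** The wording allows this; it does not report it.
- **That all active arms are affected alike.** TBWS is online and is affected only if its forms were completed after course content began.
- **That a definite minimum bias exists.** Any range that excludes zero needs a share of late baselines and a first-session shift that the article nowhere gives.

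**What to change.** 1. **Continuing recruitment.** Reconcile the abstract, Quantitative Methods, Secondary Outcomes and the consent text by requiring the week 1 questionnaire before any session 1 content, or any course content in TBWS. In practice, close the electronic link at session start, and complete paper consent and the paper form first. Setting and Timeline says that recruitment for RQ4 continues and that ethical approval runs to the end of 2028, so the rule can still take effect.
2. **Frozen data.** Classify each baseline as before, during or after session 1 from electronic time stamps where these were recorded. Flag paper forms as in-session with order unknown.
3. **Analysis.** Within the sensitivity analyses already promised under Strengths and Limitations, add one of the primary contrasts limited to baselines known to precede session 1. Report the number in each timing class by arm.

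The cost is one instruction to facilitators, one derived variable and one further analysis. The drawback is that the restricted subset is smaller and may be selected, since students who answer early on the electronic route may differ from those who consent on paper. It should support the main analysis, not replace it.

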#### Primary Outcomes

The primary outcomes are loneliness and depression (refer to Table 1 and Multimedia Appendix 1 for details). Based on previous evidence, the G4H intervention has at least equal potential to promote well-being in these areas as CBT [24].

#### Secondary Outcomes

The secondary outcomes are active group memberships, mental well-being, general well-being, anxiety, social anxiety, academic performance, health-related quality of life, use of social and health care services, intervention costs, and cost-effectiveness of the intervention (refer to Table 1 and Multimedia Appendix 1 for details).

To assess participants’ academic performance, data will be retrieved from the UH student register (Sisu student information system). Academic performance is determined by 3 outcome variables: overall accumulated study credits, the grade point average (GPA) of the study credits and the weighted GPA. When determining the weighted GPA, only completed studies that have been assessed on a numeric scale (from 1 to 5) are considered, as some courses accumulate study credits but are graded only as passed or failed. Weighted GPA is determined by the grades of each course weighted by the number of credits gained for it. The academic performance data are collected from 2 time periods: a 1-year period before and a 1-year period after starting the assigned intervention (baseline, week 1).

Cost-effectiveness analyses will apply a societal perspective by including intervention costs as well as university students’ health and social services costs. For the cost-effectiveness analyses, the facilitators will provide information on the time used for planning, executing, and assessing the sessions to evaluate the costs of the G4H intervention. Furthermore, the students in all trial arms fill out 2 questionnaires before the intervention, immediately after the intervention, and at 3-month follow-up (Table 1). The questionnaires measure health-related quality of life and self-reported use of health and social services (Table 1). The use of health and social services will be monetarized using Finnish national unit costs [62].

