Compared with the no-intervention control group, we hypothesize that all active interventions reduce students’ loneliness and depression (RQ1) and improve students’ academic performance (RQ2). However, participants in the G4H intervention will experience a more long-term reduction in loneliness than those in the other active intervention groups [24]. We hypothesize that treatment alliance [25,26] and higher fidelity to the G4H manual mediate the interventions’ outcomes (RQ4). Regarding facilitators’ characteristics, we hypothesize that their greater self-rated skills and enjoyment in therapeutic work as well as agreeableness, openness, and engagement in personality traits and interpersonal relating will be positively associated with treatment alliances and intervention outcomes; and, conversely, greater difficulties and negative feelings in therapy work will be negatively associated with treatment alliances and outcomes [27-29]. Regarding motivation (RQ4), we set our hypotheses based on the self-determination theory [30] and the integral model of treatment motivation [31]. We hypothesize that autonomous motivation to participate in the intervention predicts greater engagement and increased effectiveness, whereas controlled motivation predicts lower engagement and effectiveness. We further hypothesize that engagement partially mediates the relationship between motivation and intervention effectiveness. No preliminary hypotheses are posed regarding RQs 3 and 5.

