#### Arm 1: G4H (The Experimental Group)

G4H is a manualized group intervention that targets social group memberships with the aim of improving well-being [17], as discussed in the introduction.

The G4H intervention consists of five 90-minute sessions that aim to provide participants with the knowledge and skills they need to effectively manage their social group memberships and identities. Each of the 5 intervention sessions pertains to 1 module. Each module integrates exercises and discussions from the G4H workbook targeting various aspects of group dynamics as outlined in the SIAH and SIMIC frameworks. In brief, the first module “schooling” provides psychoeducation about the importance of social group memberships for health; the second module “scoping” supports the participants in exploring their social identities and networks; the third module “sourcing” aims at strengthening the social identities that are valued by the participant; the fourth module “scaffolding” supports making a social action plan to establish new valued group memberships; and finally, the fifth module “sustaining” aims at revisiting the intervention, discussing any potential difficulties, and encouraging the maintenance of group memberships [17]. A detailed description of the modules can be found in the G4H manual [32].

At the UH, the G4H group size can vary between 4 and 9 university students. The groups are mostly organized face-to-face, although some groups meet entirely remotely. The students earn 2 European Credit Transfer and Accumulation System (ECTS) credits for completing the G4H intervention.

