#### Arm 2: SPGs (Active Comparator 1)

The UH study psychology team organizes group interventions for various challenges related to studying for bachelor’s and master’s students. The SPGs offer client-centered peer support facilitated mostly by 2 study psychologists (some individual sessions may have only 1 facilitator). The recurring themes in the SPGs include challenges with attention, independent studying, scientific writing, and support for re-entering the studies after a break. The structure of the different thematic groups is similar—short presentations, group discussions, practices, and homework. These groups are implemented mostly as face-to-face meetings; however, in some groups, part of the meetings are conducted face-to-face and part as remote meetings. One group typically lasts for a study period and comprises five to six 90‐105 minute sessions. The typical group size ranges from 10 to 12 students. The interventions have potential in supporting study skills and the challenges of initiating study tasks, identifying and normalizing unpleasant thoughts and emotions related to studying, and acknowledging the role of one’s individual situation and well-being in study planning. The study psychologists’ work is bound by the legal and ethical requirements for licensed psychologists in Finland, overseen by the National Supervisory Authority for Welfare and Health (Valvira).

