#### Arm 3: TBWS (Active Comparator 2)

TBWS is an optional, 7-week online intervention course available for all UH students that aims to foster well-being and study skills. The course protocol has been described in detail earlier by Asikainen and Katajavuori [34]. The course is based on the principles of acceptance and commitment therapy [35] and aims to promote psychological flexibility. In addition, it aims to support study skills such as time management. The course takes place on an online learning platform (Moodle), and the students earn 3 ECTS credits for completing it. This course progresses weekly and has 6 central themes, including an introduction to the themes, individual work in practicing psychological flexibility and study skills, and weekly peer group discussions. The peer group work is an important part of the intervention and lasts throughout the course. In the peer groups, there are about 5 students in each group, and the groups remain the same throughout the course. Acceptance and commitment therapy–based interventions have been shown to support well-being among university students [36], and previous studies have suggested that this course can improve students’ well-being and studying in several ways [37,38]. Thus, participating students have the potential to benefit from this intervention in terms of increased well-being.

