#### Arm 4: The No-Intervention Control Group

The control group consists of students who are currently not taking part in any group interventions for study skills or psychological well-being at the UH. The participants in the control group may, however, take part in other social and mental health services than those provided by the UH, and this is not restricted during their participation in the study. The recruitment and data collection among the control group are scheduled to take place simultaneously with the active intervention groups: the participants are recruited at the same time, and they answer the questionnaires at the same pace as the active interventions progress during the academic year.

The interventions studied in this protocol have been developed for educational contexts and thus are expected to be well-suited for the university context. As discussed earlier, the G4H builds on SIAH and SIMIC, particularly aiming at supporting well-being during transitions in life, such as entering a university [21]. In addition, both the SPGs and the TBWS courses have been specifically developed by experts within the UH for supporting university students’ well-being and academic ability.

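### The RQ2 credit count includes the 2 ECTS (G4H) and 3 ECTS (TBWS) awarded for completing the intervention itself, which tilts that one variable towards these arms against controls unless the courses displace other study

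*Protocol article*

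**What the plan says.** All places are in the protocol article.

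- **Outcome.** Secondary Outcomes: "Academic performance is determined by 3 outcome variables: overall accumulated study credits", followed by GPA and weighted GPA. That section limits the weighted GPA to numerically graded studies, because some courses give credits on a pass/fail basis. It places no limit on which credits are counted.
- **Window.** The same section takes the data from "a 1-year period before and a 1-year period after starting the assigned intervention (baseline, week 1". Table 1 is looser: "1 year before and 1 year after the intervention (arms".
- **G4H.** "The students earn 2 European Credit Transfer and Accumulation System (ECTS) credits for completing the G4H intervention".
- **TBWS.** "the students earn 3 ECTS credits for completing it".
- **SPGs.** The arm description gives format and content ("One group typically lasts for a study period and comprises five to six 90‐105 minute sessions") and does not mention credits.
- **Controls.** They are "students who are currently not taking part in any group interventions for study skills or psychological well-being at the UH".
- **Hypothesis.** Aim and Objectives expects all active interventions, compared with no intervention, to "improve students’ academic performance (RQ2".

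**The concern.** A student who completes G4H or TBWS gains register credits for doing so, and those credits are then counted as academic performance. The register total could rise by that amount without any change in the student's other studies.

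The direction differs by contrast:

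- G4H and TBWS are favoured over controls, as hypothesised.
- G4H is disfavoured against TBWS, whose course carries one credit more.
- G4H is favoured over SPGs only if SPGs carry no credits.

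The planned methods do not address this. Propensity weighting and double-robust estimation (Statistical Analyses) deal with selection on background characteristics. This shift arises after baseline and comes from the treatment itself. Analysis by intention to treat only scales it by the share who complete.

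What is at stake is how a credit difference in RQ2 is read: it could reflect better studying, or only credit for attending.

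**Working it through.** **The plan's own figure.** The article gives no target difference, SD or power for credits. The one design figure covering RQ1-RQ3 (Sample Size: at least 95% power for f = 0.20 with 600 participants and 35% attrition) is not specific to credits. With 600 × 0.65 = 390 analysed, and assuming four measurements with correlation 0.5, a between-groups repeated-measures calculation gives power 0.993 at alpha 0.05 and 0.962 at 0.05/6. The figure is attainable under those assumptions, but it has no bearing on this point.

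**Do the credits fall in the window?** The after-year starts at week 1. G4H runs over 7 weeks and TBWS is a 7-week course, so credit for completing either would ordinarily be registered early in that year. Table 1's wording could be read as starting the year after the course, but the Secondary Outcomes text anchors it at the start.

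**Inputs from the article.** Credits: 2 (G4H) and 3 (TBWS). Enrolled: G4H 155, TBWS 216, controls 203 (Study Status).

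**Inputs assumed, because the article does not give them.** SD of yearly credits 15-25 ECTS; completion share c = 0.70-1.00; no displacement of other study; controls earn none of these credits; no true effect; unadjusted two-sided 5% test.

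**Formulas.** Shift = credits × c. SE = SD × √(1/n1 + 1/n2). Rejection rate = Φ(shift/SE − 1.96) + Φ(−shift/SE − 1.96).

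For G4H vs control, √(1/155 + 1/203) = 0.1067. For TBWS vs control, √(1/216 + 1/203) = 0.0978.

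| Contrast | SD | c | Shift (ECTS) | Shift/SD | SE | Shift/SE | Rejection rate |
|---|---|---|---|---|---|---|---|
| G4H vs control | 15 | 1.00 | 2.0 | 0.13 | 1.60 | 1.25 | 24% |
| G4H vs control | 20 | 1.00 | 2.0 | 0.10 | 2.13 | 0.94 | 15.5% |
| G4H vs control | 25 | 0.70 | 1.4 | 0.06 | 2.67 | 0.53 | 8% |
| TBWS vs control | 15 | 1.00 | 3.0 | 0.20 | 1.47 | 2.05 | 53% |
| TBWS vs control | 20 | 1.00 | 3.0 | 0.15 | 1.96 | 1.53 | 33.5% |
| TBWS vs control | 25 | 0.70 | 2.1 | 0.08 | 2.44 | 0.86 | 14% |

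**Sensitivity to displacement.** If half the course credits replaced other study (SD 20, c = 1), the shifts halve to 1.0 and 1.5 ECTS. Shift/SE becomes 0.47 and 0.77, and the rejection rates about 8% and 12%. With full displacement the shift is 0 and the rate is the nominal 5%.

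**G4H vs TBWS.** With equal completion the shift is (2 − 3) × c, that is −0.7 to −1.0 ECTS. With unequal completion it runs from 2 × 1.0 − 3 × 0.7 = −0.1 to 2 × 0.7 − 3 × 1.0 = −1.6.

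**The case against.** The strongest case on the other side has five parts.

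1. **Displacement.** A reader might infer that completers end the year exactly 2 or 3 credits ahead of controls. The documents do not support that. It requires the course to come on top of a student's usual load, and the article has no data on this. The objection stands: the true lower bound is no bias.

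2. **Comparators.** A reader might take it as fact that G4H is favoured over SPGs. The article's silence on SPG credits does not show that none are awarded. Controls, too, need only be outside such groups currently, and TBWS is open to all students of the university, so some may take it within the year. Both points stand.

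3. **The rejection rates.** They come from an unadjusted test with an assumed SD. Weighting may widen the standard error and multiplicity control would lower rejection, while adjustment for prior credits would narrow the standard error. The rates are illustrations only.

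4. **Scope.** A reader might infer that all of RQ2, or the trial's main conclusions, are compromised. The article does not support that. The primary outcomes are loneliness and depression, academic performance is a secondary outcome, and credits are one of its three variables. The GPA measures are affected only if a course is numerically graded, which is not stated.

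5. **Condensed article.** Register filters are often left to a fuller document. This part does not succeed: the article itself fixes both the outcome, as the overall total, and a window starting at week 1. An analyst following it would count the course credits.

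**Conclusion.** The point holds for the credit variable of RQ2. As defined, the count includes credits for completing two of the interventions, and no planned method takes them out. That follows from the text alone.

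The size does not. The gross shift is at most 2 ECTS (G4H) or 3 ECTS (TBWS) times the completion share. Under the stated assumptions this is 0.06-0.13 SD and 0.08-0.20 SD against controls, with false rejection of about 8-24% and 14-53%. Displacement of other study, or later uptake by controls, reduces both figures, down to no shift and 5%. The shift against G4H relative to TBWS is about 1 ECTS at full and equal completion. The shift for G4H over SPGs is conditional on SPGs carrying no credits.

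It would go too far to say that a positive credit result must be an artefact; the outcome as defined simply cannot separate the two explanations. This is a should-fix: a clear flaw in one secondary variable, with RQ1 untouched.

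**What to change.** In Secondary Outcomes, define the main credit outcome as register credits excluding the studied intervention courses: G4H, TBWS and any SPG that carries credits. Apply the exclusion to both the before and after windows and to all four arms. Both windows matter because the Figure 2 caption identifies students who had already taken part in the same or another arm, and TBWS is open to everyone, so course credits can also sit in the baseline year or in the control arm.

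Report the overall total alongside as a sensitivity analysis. Excluding course credits could understate G4H and TBWS if the course replaced other study, so the two counts together show how far the result depends on displacement.

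State whether SPGs carry credits and whether any of the courses is graded numerically; if one is, apply the same exclusion to the GPA measures. Align the window wording in Table 1 with the text.

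The cost is a short change to the definition and a course-code filter on the register extract. RQ2 analyses are planned for 2026 to 2027, so the filter can be set before they begin, and no new data collection is needed.
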